**Design:**

This is a multicenter randomized controlled trial in France comparing the efficacy of biliary reconstruction with or without a removable intraductal stent on reducing biliary complications. Inclusion and randomization are performed during LT when a duct-to-duct biliary anastomosis smaller than 7 mm in diameter is envisioned. In the intraductal stent group, a custom-made segment of a T-tube is placed into the bile duct and removed endoscopically 4 to 6 months later. The surgical technique is described in a video during randomization and is available on the secure website used for inclusion and randomization. The primary endpoint is the occurrence of biliary complications, including biliary fistulae and strictures, during the 6 months of follow-up. Secondary evaluation criteria are the incidence of complications related to the stent placement and its extraction by endoscopy. The inclusion of 248 patients in total has been determined based on an expected incidence of biliary complications of 25 % in the non-IST group and a 60 % reduction of biliary complications (10 %) in the IST group.

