## Background

Biliary tract reconstruction during liver transplantation (LT) is the final technical step and the cornerstone of the procedure and is often performed by a duct-to-duct anastomosis. Rarely, recipient and donor biliary stump discrepancies or liver disease-related reasons could lead to a hepaticojejunostomy. The proper completion of this technical step is crucial for postoperative outcome [1, 2]. The incidence of biliary complications following liver transplantation (LT) remains high, ranging from 10 to 50 % of patients among clinical series despite an increasing experience worldwide [2–4]. These complications, mainly represented by biliary leaks and biliary strictures, are responsible for substantial post-transplantation morbidity and graft loss. Biliary leakage occurs mostly within 3 months postoperatively. This early complication reaches a 10 to 20 % incidence rate [3, 4]. Biliary strictures mainly occur later, within 5 to 8 months and up to 1 year in most. The reported incidence of biliary strictures still ranges from 5 to 30 % among large and recent clinical series [2, 4].

The use of an external T-tube to reduce biliary complications has been debated for decades [5–10]. The initial rationale was to facilitate biliary healing and maintain easy access to the biliary tract to perform a cholangiography until removal of the T-tube in consultation, in general within 6 weeks post-transplantation [11]. However, specific complications related to the cholangiography, such as cholangitis, and the development of endoscopic techniques, have reduced its legitimacy. Moreover, numerous published studies [5–8, 10], including three randomized studies [6–8], have shown not only an absence of difference of biliary complications with or without the T-tube use but also a specific morbidity related to the T-tube, such as cholangitis, and biliary leaks at the time of removal.

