### Study course

The study is a multicenter, prospective, randomized controlled study. The follow-up is set at 6 months postoperatively to screen the majority of biliary complications. The inclusion period is set at 2 years, for a total study duration of 2.5 years.

The patient inclusion will be made in seven liver transplantation centers in France.

Definitive inclusion will take place in the operating room, during LT, and depends on fulfillment of the indicated “definitive inclusion criteria” (see above).

The randomization will be performed in the operating room by the investigator and coordinated by the Clinical Research Unit of the promoters’ center (Saint Antoine Hospital, Paris), with specific software accessible on the Internet.

In the IST group, the surgeon will place the IST in the bile duct, which is a custom-made segment (2 cm) of an 8 Charrière T-tube. The stent is inserted in the biliary duct without suture fixation (Fig. 1).

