**Fig. 1 Fig1:**
[figure not shown]
Intraductal stent tube insertion (short movie extracts)

To minimize bias and homogenize the technique, a short technical explanatory movie was developed by the principal investigator’s team and provided on the internet. The technique of biliary reconstruction by either running suture or interrupted stiches is left to the surgeon preference because no impact has been demonstrated on the occurrence of biliary complications.

Each center performs its habitual postoperative follow-up. Clinical, biological, and radiological data are collected at Day 1, Day 7, Day 15, Month 1, Month 3, and Month 6. A Magnetic Resonance Cholangiography (MRC) is performed at 6 months post-LT, which is after the stent removal.

In the IST group, an endoscopic retrograde cholangio-pancreatography (ERCP) with sphincterotomy is planned between the 4^th^ and the 6^th^ month post-transplantation, requiring a short stay in the hospital, a general anesthesia, and clinical and biological tests including plasmatic lipase dosage at Day 1.

Every undesirable event will be immediately reported to the sponsor for further investigation of its severity. Severe undesirable events are previously defined.

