### Statistical analysis

The inclusion of 248 patients in total has been estimated based on an expected incidence of biliary complications of 25 % in the non-IST group, and a 60 % reduction of biliary complications (10 %) in the IST group with an alpha risk of 5 % and a beta risk of 20 %.

The statistical analysis will be in an intention-to-treat fashion. The frequency of occurrence of a biliary complication will be compared between groups with a χ^2^ test or a Fisher test as appropriate.

Adjusting factors such as arterial thrombosis or surgical technique will be managed with logistic regression models as appropriate.

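### The supplementary logistic regression names adjusters that can arise or be chosen after randomisation (arterial thrombosis, surgical technique); the primary unadjusted test is unaffected.

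*Protocol article*

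**What the plan says.** All references are to the protocol article.

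- **Main comparison (Statistical analysis).** "The statistical analysis will be in an intention-to-treat fashion", and "The frequency of occurrence of a biliary complication will be compared between groups with a" χ² or Fisher test. No covariates enter it.
- **Adjustment (same section).** "Adjusting factors such as arterial thrombosis or surgical technique will be managed with logistic regression models as appropriate". These are the only two covariates that the article names. It neither dates arterial thrombosis nor defines surgical technique.
- **Timing of randomisation.** Design (Abstract): "Inclusion and randomization are performed during LT when a duct-to-duct biliary anastomosis smaller than 7 mm in diameter is envisioned". Study course: "The randomization will be performed in the operating room by the investigator". Background: "Biliary tract reconstruction during liver transplantation (LT) is the final technical step".
- **Choice of suture (Study course, text after Fig. 1).** "The technique of biliary reconstruction by either running suture or interrupted stiches is left to the surgeon preference", on the ground that no effect on biliary complications has been shown.
- **Eligibility (Patient selection).** Arterial thrombosis is neither an inclusion nor an exclusion criterion, and nowhere is it listed as a baseline variable.

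**The concern.** A covariate-adjusted estimate keeps the protection of randomisation when the covariates are fixed before allocation. If a covariate can be influenced by the arm, conditioning on it does two things. It removes whatever part of the effect runs through that covariate, and it can create an association between arm and outcome through causes that the covariate and the outcome share. The result no longer estimates the intention-to-treat effect that the same section promises.

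Both named factors are open to this. At stake is how the trial's adjusted odds ratio is read. If the stent changed the frequency of thrombosis, the adjusted figure could make it look better or worse than it is, beside an unadjusted result that is correct.

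**Working it through.** **Step 1. Place each factor in time.**

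- Randomisation takes place in theatre, when the anastomosis is still only planned. Biliary reconstruction is the last technical step. The suture is therefore made after allocation.
- The surgeon inserts the stent in the stent arm and so knows the arm when choosing the suture.
- Nothing limits arterial thrombosis to events before allocation, and follow-up lasts 6 months. As written, the covariate takes in thromboses during follow-up. An occlusion recognised before allocation would be a baseline factor, but the text makes no such restriction.

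**Step 2. Illustrate the effect on the odds ratio (OR).** The article gives no thrombosis rate and no risk after thrombosis, so every input here is an assumption. Take a 70 % biliary complication risk after thrombosis in both arms. With thrombosis rate t and risk r without thrombosis, the arm's risk is p = 0.70·t + r·(1 − t). The unadjusted OR is [p₁/(1 − p₁)] / [p₀/(1 − p₀)], where 1 is stent and 0 is control. The adjusted OR comes from a logistic model with arm and thrombosis, fitted to the expected cell frequencies.

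| t control / stent | r control / stent | p₀ | p₁ | Unadjusted OR | Adjusted OR |
|---|---|---|---|---|---|
| 4 % / 8 % | 22 % / 10 % | 0.2392 | 0.1480 | 0.552 | 0.426 |
| 8 % / 2 % | 20 % / 12 % | 0.2400 | 0.1316 | 0.480 | 0.564 |
| 4 % / 4 % | 23 % / 8 % | 0.2488 | 0.1048 | 0.353 | 0.319 |
| 4 % / 4 % | 22 % / 10 % | 0.2392 | 0.1240 | 0.450 | 0.419 |

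First row in full: p₀ = 0.70 × 0.04 + 0.22 × 0.96 = 0.2392; p₁ = 0.70 × 0.08 + 0.10 × 0.92 = 0.1480; OR = (0.1480/0.8520) / (0.2392/0.7608) = 0.552.

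The first two rows show that the shift can go either way. In the last two, allocation does not affect thrombosis. Their smaller gaps are non-collapsibility (a conditional OR differs from a marginal one) and not bias.

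**Step 3. Separate bias from a real effect.** Suppose the stent has no direct effect and the control rate is 25 %. Assume control thrombosis of 3 to 10 %, an OR of 6 for thrombosis on biliary complications, and an unmeasured binary cause (present in half of patients) with an OR of 4 on each of the two.

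- Stent does not alter thrombosis: unadjusted and adjusted OR are both 1.00.
- Stent alters thrombosis (OR 0.5 to 3): the total OR runs from 0.91 to 1.31, the adjusted OR from 0.94 to 1.02.
- Extreme case, 10 % control thrombosis and OR 3: total OR 1.31, adjusted 0.94. A net harm would appear as a slight benefit.

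**Step 4. Is adjustment needed for power?** With 248 patients (1:1 assumed, so 124 per arm), 25 % versus 10 % and two-sided α of 5 % (assumed), the pooled rate is 0.175. The null standard error is √(2 × 0.175 × 0.825/124) = 0.0483, and the alternative one is √((0.25 × 0.75 + 0.10 × 0.90)/124) = 0.0473. Power = Φ[(0.15 − 1.96 × 0.0483)/0.0473] = 0.88. An exact calculation for Fisher's test gives 0.85. Both exceed the planned 0.80, so the unadjusted test does not need these covariates.

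**The case against.** - **The planned comparison is sound.** The χ² or Fisher test comes first, is by intention to treat and uses no covariates. The regression is a separate, conditional sentence. This stands in full and limits the point to the regression. A reader might infer that the trial's efficacy result is itself not a randomised comparison; the text does not support that.
- **No licence to substitute.** A reader might infer that the sponsor may present whichever result is more favourable. The article does not say so, and an article may leave the model's rank and its full covariate list to the analysis plan, which is not shown. What remains is that the two covariates it does name are poor choices for an efficacy model.
- **Suture technique.** Surgical technique is undefined, and reading it as running versus interrupted suture is an inference. A surgeon's habit may also predate allocation. Both objections stand as limits, but the suture is the only choice of technique that the article describes, and it is made with the arm known.
- **No self-contradiction.** A reader might see a conflict between adjusting for technique and leaving it free because "is left to the surgeon preference because no impact has been demonstrated on the occurrence of biliary complications". An effect not demonstrated is not an effect excluded, so checking the factor in a model is coherent.
- **Plausibility.** The article suggests no stent effect on the hepatic artery; its anticipated complications are biliary, endoscopic and digestive. This stands. The first two table rows show what is possible, not what is likely.

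**Conclusion.** The point holds for the supplementary logistic regression only. It names as adjusters one factor that, as written, includes post-randomisation events, and another that, on its natural reading, is chosen after allocation by an unblinded surgeon. If allocation affects either, the adjusted odds ratio is not protected by randomisation.

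The size in this trial cannot be computed from the document. The odds ratios shown rest on assumed thrombosis rates and an assumed stent effect on thrombosis; without such an effect there is no bias under the null. The post-randomisation status of thrombosis is inferred from the timing of randomisation and the absence of any restriction, since the article does not date it. Because the primary comparison stays valid, this should be fixed but does not undermine the trial.

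**What to change.** In the Statistical analysis section:

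1. State that the unadjusted intention-to-treat χ² or Fisher test is the primary efficacy result.
2. Limit any adjusted efficacy model to prespecified factors fixed before randomisation, for example centre and graft and recipient bile-duct diameter, and remove arterial thrombosis and suture technique from it.
3. Report arterial thrombosis by arm as an outcome, and suture technique by arm descriptively.
4. Label any model that includes either factor exploratory, and do not use it for the efficacy conclusion.

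The cost is a few sentences. The change needs no extra patients and leaves the sample size as it is. If the analysis plan already says this, it is enough to bring the article's sentence into line.

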### Ethical approval

This trial has been approved by the *Comité de Protection des Personnes (CPP)* Ile de France III - 3170 (File ref: 2014-A00866-41).

## Discussion

Despite a global improvement in overall survival rates in LT in the last decades, decreasing the incidence and severity of biliary complications remains a major goal for transplant surgeons.

External drainage using T-tube has not proven its efficacy in a consensual way. Still debated, T-tube placement is not used anymore in numerous teams because of the nonproven preventative effect on biliary complications and because of the specific complications related to its use and removal, such as bile leaks and cholangitis [5–8, 10]. Moreover, such a hypothetic prevention of biliary complication is not supported by the fact that T-tubes are removed early, within the initial 2 months postoperatively. This delay is probably too short to prevent the development of a biliary stricture. This lack of long-term effect may be advantageously cleared by the IST technique. This innovative, easy to reproduce technique allows a longer stenting effect on biliary reconstruction and avoids specific morbidity related to the external biliary drainage [18].

Specific complications related to endoscopic extraction of the stent and ERCP with sphincterotomy, in general, may be expected in this study. However, large clinical studies report very low complication rates; in the study of Cotton et al. (2009), in an analysis of more than 11,000 procedures, the overall complication rate was about 4 %, with very low incidence of hemorrhage (0.3 %) or acute pancreatitis (2 to 3 %) [20]. In our preliminary study carried out on 20 patients, no technical failures and no procedure-related complications were recorded during drain removal. A limited sphincterotomy was performed in 17 patients of 20 without any complication [18]. The small number of patients and the single-center referring to an experienced endoscopist may also explain these results.

Some complications specific to the stent may also be expected, such as stent migration in the duodenum, infectious cholangitis, or extraction difficulties due to stent incrustation. In our experience, one cholangitis occurred and was successfully treated by antibiotics and drain removal. This latter patient had a transpapillary drain that may explain the occurrence of a backflow into the biliary tract [18]. Consequently, we decided to systematically place the tube above the ampulla of Vater. One patient experienced a clinical asymptomatic spontaneous migration of the stent in the duodenum, without any consequences. No difficulties were recorded during IST ablation because of stent incrustation, event after more than a 6-month postoperative delay.

We previously performed this technique in patients with a graft bile duct diameter less than 5 mm. This option was based on several studies [12, 21–23] that demonstrated a significant association between the risk of biliary stenosis and the small diameter of the biliary duct. Asian studies [21–23] found a significantly increased risk for less than 5 mm bile duct diameter, but these studies are conducted on reduced liver grafts obtained from living donors. A recent trial [12] found a significantly increased risk for bile ducts less than 7 mm in diameter in 197 transplanted patients from whole cadaveric liver grafts. Thus, a cut-off value of 7 mm for graft bile duct diameter was chosen for this trial.

In the design of this trial, we assumed an expected biliary complication rate in the non-IST group of 25 %. We considered that these patients with a small bile duct diameter (<7 mm) presented a higher risk of biliary strictures, according to the literature. A 60 % reduction in biliary complications, representing a 10 % biliary complication rate in the IST group, seemed to be a reasonable goal.

To avoid any bias related to technical issues and given the multicenter design of the trial, we decided to produce a movie that clearly explains the procedure step-by-step. To our knowledge, this is the first time that such a technical standardization has been used in the surgical research field, especially its accessibility on the Internet, which means it always available during the randomization in the operating theatre. This technique will be available on a secure website that is already being used for inclusion and randomization, and later will be attached to the publication of the results. This innovative form of surgical diffusion will be useful to avoid technique bias and to standardize the technique worldwide when published.

In conclusion, this randomized, multicenter controlled trial aims at validating this technique as a safe, innovative way to prevent biliary complications in high-risk patients following liver transplantation.

## Abbreviations

ERC: endoscopic retrograde cholangiography
IST: intraductal stent tube
LT: liver transplantation
MRC: magnetic resonance cholangio-pancreatography
